### Combination therapies

■ We prefer that enrolled subjects with mild sleep difficulties not receive any sleeping pills. Zolpidem, zopiclone or estazolam will be prescribed for patients with severe insomnia disorders■ Enrolled subjects with other physical illnesses will continue with their original treatment plan■ Considering the precision of our collected clinical outcome data, antipsychotics, ADs or mood stabilizers (e.g., sodium valproate, lithium carbonate) will not be allowed to be prescribed during the study period. Similarly, any drugs that could have interactions with our study drugs, such as antiarrhythmic or antidiabetic drugs or tryptophan, will not be administered either■ The participants’ treatment history and concomitant treatments should be recorded on the CRF

### Adherence

Before obtaining written informed consent, the patients will be comprehensively briefed on both the importance of conducting this clinical study and the value of their participation. Specifically, detailed information on our study procedure, its potential risks and its effectiveness will be conveyed to the subjects. Moreover, the economic burden of taking ADs can be partially alleviated, and subsidies, supported through funding, will be paid after they accomplish their follow-up assessments. During hospitalization, study drugs and doses will be monitored by the research nurse. Thus, medication compliance will be guaranteed. After discharge, the drug regimen and follow-up arrangement will be explained to the patients. The physician-patient relationship will be built on mutual respect and trust.

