## Abstract

**Background:**

Major depressive disorder (MDD) is a common psychiatric disorder. With systematic antidepressant treatment, 50–75% of patients have a treatment response but require 4–6 weeks to have their symptoms alleviated. Therefore, researchers anticipate the development of novel fast-acting antidepressants. Previous studies have revealed that the decrease of bio-energetic metabolism may contribute to the occurrence of depression, while our team has found adenosine triphosphate (ATP) and phosphocreatine (PCr) to be fast-acting antidepressants in the depressed-animal model. ATP and PCr have already been widely prescribed clinically as energy supplements for cells. This will be the first clinical attempt of the intravenous administration of ATP and PCr combined with orally administered fluoxetine in MDD.

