Studies around MDD and mitochondrial activity or ATP synthesis have been conducted and proved to be relevant [17–22]. Approximately 54% of subjects diagnosed with a mitochondrial disease have comorbid MDD. “Mitochondrial cocktails” for the treatment of mitochondrial diseases, CoQ10/creatine in particular, also exert AD-like effects [23]. When treated with CoQ10 for 21 days, rats exposed to chronic restraint stress showed improvement both in the forced swimming test and the open-field test [24]. Clinically, a 4-week treatment of CoQ10 in geriatric bipolar depression resulted in a significant reduction in Montgomery Asberg Depression Rating Scale scores [25]. In an 8-week study of oral treatment with creatine, female adolescents with SSRI-resistant MDD showed a steady decrease in Children’s Depression Rating Scale-Revised (CDRS-R) scores and a significant increase in PCr in the brain on ^31^P magnetic resonance spectroscopy [26].

The limited reservoir of ATP in the brain demands a high re-synthesis rate to fuel vast energy requirements, accounting for approximately 20% of all energy production. In contrast, PCr, stored abundantly in the brain, transiently transfers high-energy phosphoryl bonds to form ATP through the activity of creatine kinase (CK). Thus, the continuous supply of the high-energy phosphoryl bonds by PCr appears to contribute to the dynamic equilibrium of ATP consumption and ATP synthesis [27].

In our preclinical studies, the ATP levels were significantly decreased in artificial cerebral spinal fluid, as well as in the interstitial fluid in the hippocampus and PFC, collected in susceptible mice but not in unsusceptible mice after chronic social-defeat stress. Lateral intracerebroventricular injection of ATP reduced total immobility time in the forced swimming test. Furthermore, 7-day intraperitoneal injections of ATP yielded AD-like effects to an extent similar to that of 28-day treatment with imipramine [28]. Additionally, intraperitoneal injection of PCr in the depressed rats at multiple dosages (31.25, 62.5, 125, 250 mg/kg) achieved remarkable AD effects, with 125 mg/kg PCr producing the best efficacy.

Together, the researches highlight a pivotal connection between reduced levels of ATP/PCr and depression. For this reason, we hypothesized that ATP and PCr may be potential fast-acting ADs in the treatment of MDD.

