**Table Taba:** 

Outcomes	
Recruitment period	
Feasibility outcomes	Our pilot study will be conducted in a general hospital. The difficulties while recruiting will be recorded and discussed in the final report. Regarding our study inclusion criteria, moderate to severe MDD patients with HAMD-24 ≥ 20 can be enrolled. Some of our eligible patients might be inclined to choose non-pharmacological treatment. The percentage of eligible patients refusing to participate in our study. Their reason will be recorded on the recruitment document and discussed in the final report. The percentage of eligible patients willing to participate in our study. Their reason will be recorded on the recruitment document and discussed in the final report
recruitment difficulties	
eligibility rate	
intention to use medication	
refusal rate	
participation rate	
Study period	
Feasibility outcomes	While hospitalized, the drug compliance will be guaranteed by bedside nurses. The assessment of adherence rate will follow schedule and their reason for not taking drugs will be recorded. (see Fig. 2). The percentage of enrolled patients withdrawn before completion of our study. Their reason will be recorded on the Case Report Form (CRF). If “yes,” the researcher should list the name/dosage/duration, and explain its reason for use on the CRF. After study period, the percentage of enrolled patients willing to receive medical advice from our clinical researcher. The occurrence rate of side effects or the adverse events. Test the conduction of our blinding method
adherence	
withdrawn	
concomitant therapy	
retention	
side effects/adverse events	
blinding	
Overall	
Feasibility outcomes	At any time of their participation, enrolled patients will be encouraged to report their suggestion or feeling to researcher. Also, they will receive a questionnaire questioning their perceptions toward the medical environment, treatment response, sense of security and suggestion while hospitalized. It will be recorded and discussed in final report. The appropriateness of the implementation of our study scheme and it will be discussed in final report
participation/hospitalization feedback	
study scheme	

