### Study efficacy outcomes

The efficacy outcome measure will be assessed by both clinician-rated HAMD-24, Clinical Global Impression (CGI) Scale and self-rated PHQ-9. HAMD-24, a well-established representative scale for patient selection and follow-up assessments, has been selected to indicate the alteration in patients’ clinical symptoms both overall and in each subset item after treatment. When using this 24-item scale, a patient with the total score over 20 or higher will be considered to be suffering from moderate, severe or very severe depression [36–38]. This scale comprises 24 items indicating seven subsets includes: (1) anxiety/somatic symptoms; (2) weight alteration; (3) cognitive disorder; (4) diurnal symptom; (5) retardation; (6) insomnia; (7) helplessness and worthlessness and hopelessness [39]. The CGI is a 7-point scale, with a score based on the physician’s medical knowledge and experience regarding the patient’s general psychiatric condition. It includes the evaluation of the illness severity from 0 (normal) to 7 (the most severely ill) prior to therapy and two more aspects which are the therapeutic response and change from 1 (very much improved) to 7 (very much worse) after receiving medical treatment [40]. The Patient Health Questionaire-9 items (PHQ-9) is a self-reported questionnaire range from 0 to 27, each of the nine questions can be scored from 0 (not at all) to 3 (almost every day) according to the presence and severity of depression over past 2 weeks. It categorizes depression severity according to scores of 0–4 (none to minimal), 5–9 (mild), 10–14 (moderate), 15–19 (moderately severe) and 20–27 (severe) [41]. The Side Effects Rating Scale (SERS) of Asberg assesses the unwanted effects accompanied by antipsychotic drugs weekly, questions around the severity of increased fatigability, headache, insomnia, dizziness, orthostatic syncope, palpitations, tremor, increased tendency of sweating, reduced salivation, constipation, urination disorder, sleepiness, sexual dysfunction, and others. Its scores ranges from 0 (absent) to 3 (among the most severe) [42].

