## Discussion

Multiple studies have revealed altered energy metabolism in brain regions. With the utilization of in-vivo phosphorous magnetic resonance spectroscopy, nucleoside triphosphate (NTP), which mainly derives from ATP, has shown to be decreased in depressed subjects [45]. Meanwhile, in MDD patients treated with either SSRI sertraline, or creatine, or thyroid hormones, which have been shown to increase brain bio-energetic metabolism, NTP levels are significantly increased in treatment responders compared with non-responders [26, 46, 47]. Compared with conventional ADs, novel compounds with fast-acting AD effects will minimize the time lag to obtain treatment results, enhance patients’ adherence, reduce the suicide rate and aid psychosocial recovery.

Our preclinical studies showed that ATP, as well as PCr, displayed rapid AD effects in animal models of depression. To our knowledge, our study is the first clinical attempt to add ATP/PCr intravenously with the orally administered fluoxetine to patients with moderate to severe MDD.

PCr, after being diluted in 0.9% saline 100 ml, should be infuse intravenously within the next 40 min. As this is a double-blinded experiment, both ATP and placebo group should be administered in less than 40 min. However, if the infusion rate of ATP is too fast, some patients might experience palpitations. We assume that the nocebo effects might influence the efficacy results in ATP group.

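### The pre-consent briefing is to convey effectiveness, although the protocol treats the effect of add-on IV ATP or PCr in MDD as untested in patients

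*Protocol article*

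**What the plan says.** Under Adherence, the protocol article describes the information given at recruitment: "Before obtaining written informed consent, the patients will be comprehensively briefed". The same paragraph then specifies that "detailed information on our study procedure, its potential risks and its effectiveness will be conveyed to the subjects", and goes on to mention partial relief of drug costs and subsidies paid after follow-up.

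Elsewhere the article describes the evidence differently. The Abstract states: "This will be the first clinical attempt of the intravenous administration of ATP and PCr combined with orally administered fluoxetine in MDD". The Discussion repeats that "our study is the first clinical attempt to add ATP/PCr intravenously". The Background ends with "we hypothesized that ATP and PCr may be potential fast-acting ADs in the treatment of MDD". Research objectives limits efficacy to a preliminary exploration. Consent or assent lists what the consent form covers, including the treatment plan, side effects and expenses; effectiveness is not on that list.

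Two groups of outcomes could be affected. On efficacy: "The efficacy outcome measure will be assessed by both clinician-rated HAMD-24, Clinical Global Impression (CGI) Scale and self-rated PHQ-9". On feasibility, the outcomes table includes the refusal rate and the participation rate, the latter defined as "The percentage of eligible patients willing to participate in our study".

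**The concern.** A statement about effectiveness made before consent can act in two places.

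The first is the decision to take part. Refusal and participation are settled directly after the briefing and before allocation, so neither randomisation nor blinding protects them. The Discussion says the feasibility assessment will help decide whether a full-scale trial is run. A rate obtained after an unsupported statement of benefit may not carry over to a trial with an accurate briefing.

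The second is expectancy in the symptom scales. PHQ-9 is self-rated. Data management and monitoring says that HAMD-24 is scored mostly from joint interviews with the patient and that CGI draws partly on interview. If expectancy raises improvement in every arm, there may be less room for ATP or PCr to separate from saline, and the efficacy trends are meant to inform the size of the next trial.

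**Working it through.** The plan contains no figure on expectancy, placebo response or expected participation, so the check is mainly one of text and reasoning.

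**1. What there is to convey.**
- Adherence: the briefing covers the procedure, its risks and its effectiveness.
- Abstract and Discussion: first clinical attempt of these infusions with fluoxetine in MDD.
- Background: the antidepressant effect is a hypothesis. It draws on the authors' animal work and on human data for other agents or routes (CoQ10 in geriatric bipolar depression, oral creatine in adolescents with SSRI-resistant MDD). None of these human data concern intravenous ATP or PCr.
- Consent or assent: effectiveness is not among the listed contents.

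The Adherence sentence therefore does not agree with the other sections as far as the infusions are concerned.

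**2. Effect on the between-arm contrast.** Let μ_A and μ_S be the mean scores under ATP and saline with a neutral briefing, and let the briefing lower every patient's score by e.
- Contrast in scores: (μ_A − e) − (μ_S − e) = μ_A − μ_S. The shift cancels.
- The primary measure divides the change by the baseline score B, so the shift becomes −e/B for each patient. Randomisation gives B the same expected distribution in each arm, so this also cancels in expectation.
- The same argument holds for PCr against saline, and for the ANCOVA comparisons under Statistical analyses.

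**3. When it would not cancel completely.** Suppose instead that the drug removes a fraction f of the symptoms that remain, R. The contrast is f × R with a neutral briefing and f × (R − e) with raised expectancy. It shrinks by f × e. The direction is towards no difference, not towards either infusion. The documents give neither f nor e, so no value can be computed.

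**4. Effect on participation.** The participation rate is the number willing divided by the number eligible. If the briefing changes the decision of some eligible patients, the numerator rises by that number and refusals fall by the same number. The documents do not say how many that would be.

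**5. Facts needed for a neutral statement.** Randomization and allocation concealment gives 42 patients at 1:1:1, so 42 / 3 = 14 per arm and one patient in three receives saline. Interventions says that all patients receive fluoxetine.

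**The case against.** The strongest reply is that one word in a condensed article is being made to carry too much. Grammatically, *its* refers to the study procedure. That could mean the whole regimen, and every patient receives fluoxetine; the Background reports that 50–75% of patients improve on adequate first-line drug treatment. The briefing script is not shown, the consent content makes no effectiveness claim, and the consent form went through ethics review. This part stands: the documents do not show that patients are told ATP or PCr works. Even so, the same pronoun governs the risks, which must include those of the infusion. The sentence does not separate the known benefit of fluoxetine from the unknown benefit of the add-on, so it needs clarifying on either reading.

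A reader might infer that the briefing biases the comparison in favour of the infusions. The documents do not support that. The briefing precedes allocation, and Blinding covers patients, clinical researchers and bedside nurses, so an equal shift cancels. Unequal action would need patients to recognise their infusion. The Discussion does raise palpitations with fast ATP infusion and adds: "We assume that the nocebo effects might influence the efficacy results in ATP group". But that is unblinding by infusion sensations. It could occur under a neutral script too, a nocebo effect would work against ATP, and blinding is already a feasibility item to be tested. A point estimate built on assumed recognition rates would measure that problem and not this one.

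A reader might also infer that participation is known to be inflated. It would be higher only relative to a neutral briefing, which the protocol does not set as its benchmark. Subsidies and reduced drug costs also encourage participation, and the two rates are 2 of 13 listed feasibility items, with no ranking among them.

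**Conclusion.** The concern holds as an inconsistency within the protocol with possible, unquantified consequences. The instruction to convey effectiveness before consent conflicts with the article's own account that the effect of intravenous ATP or PCr in MDD has not been tested in patients.

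The firmer consequence is for feasibility: the briefing may raise participation and lower refusal, and the design does nothing to offset this. The weaker one is for efficacy: response may rise in all arms and the contrast may narrow, with no arm favoured. The efficacy part rests on two assumptions: that staff follow the sentence literally, and that the drug effect depends on how many symptoms remain. If the effect is purely additive, the contrast is unchanged. No size can be given for either consequence. The sample size and the analysis model are not affected.

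**What to change.** In the Adherence section, replace the reference to effectiveness with a short standard statement used by all recruiting staff: the effect of ATP or PCr infusion in MDD is not known and is what the trial explores; one patient in three receives saline; all patients receive fluoxetine. This agrees with Research objectives, Interventions, Randomization and allocation concealment, and the consent content under Consent or assent.

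The cost is small but not nil. Protocol amendments requires re-approval by the ethics committee and the sponsor for changes that concern study conduct or potential benefit to patients, so notification alone is not enough. Recruitment may be slightly slower. Because Trial status says recruitment is ongoing, a change now would mix two briefings; participation and refusal should therefore be reported separately by the briefing used. No change to treatment, sample size or analysis model is needed.

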### Outcomes

#### Study feasibility outcomes

Feasibility evaluation includes

**Table Taba:** 

Outcomes	
Recruitment period	
Feasibility outcomes	Our pilot study will be conducted in a general hospital. The difficulties while recruiting will be recorded and discussed in the final report. Regarding our study inclusion criteria, moderate to severe MDD patients with HAMD-24 ≥ 20 can be enrolled. Some of our eligible patients might be inclined to choose non-pharmacological treatment. The percentage of eligible patients refusing to participate in our study. Their reason will be recorded on the recruitment document and discussed in the final report. The percentage of eligible patients willing to participate in our study. Their reason will be recorded on the recruitment document and discussed in the final report
recruitment difficulties	
eligibility rate	
intention to use medication	
refusal rate	
participation rate	
Study period	
Feasibility outcomes	While hospitalized, the drug compliance will be guaranteed by bedside nurses. The assessment of adherence rate will follow schedule and their reason for not taking drugs will be recorded. (see Fig. 2). The percentage of enrolled patients withdrawn before completion of our study. Their reason will be recorded on the Case Report Form (CRF). If “yes,” the researcher should list the name/dosage/duration, and explain its reason for use on the CRF. After study period, the percentage of enrolled patients willing to receive medical advice from our clinical researcher. The occurrence rate of side effects or the adverse events. Test the conduction of our blinding method
adherence	
withdrawn	
concomitant therapy	
retention	
side effects/adverse events	
blinding	
Overall	
Feasibility outcomes	At any time of their participation, enrolled patients will be encouraged to report their suggestion or feeling to researcher. Also, they will receive a questionnaire questioning their perceptions toward the medical environment, treatment response, sense of security and suggestion while hospitalized. It will be recorded and discussed in final report. The appropriateness of the implementation of our study scheme and it will be discussed in final report
participation/hospitalization feedback	
study scheme	

### Study efficacy outcomes

The efficacy outcome measure will be assessed by both clinician-rated HAMD-24, Clinical Global Impression (CGI) Scale and self-rated PHQ-9. HAMD-24, a well-established representative scale for patient selection and follow-up assessments, has been selected to indicate the alteration in patients’ clinical symptoms both overall and in each subset item after treatment. When using this 24-item scale, a patient with the total score over 20 or higher will be considered to be suffering from moderate, severe or very severe depression [36–38]. This scale comprises 24 items indicating seven subsets includes: (1) anxiety/somatic symptoms; (2) weight alteration; (3) cognitive disorder; (4) diurnal symptom; (5) retardation; (6) insomnia; (7) helplessness and worthlessness and hopelessness [39]. The CGI is a 7-point scale, with a score based on the physician’s medical knowledge and experience regarding the patient’s general psychiatric condition. It includes the evaluation of the illness severity from 0 (normal) to 7 (the most severely ill) prior to therapy and two more aspects which are the therapeutic response and change from 1 (very much improved) to 7 (very much worse) after receiving medical treatment [40]. The Patient Health Questionaire-9 items (PHQ-9) is a self-reported questionnaire range from 0 to 27, each of the nine questions can be scored from 0 (not at all) to 3 (almost every day) according to the presence and severity of depression over past 2 weeks. It categorizes depression severity according to scores of 0–4 (none to minimal), 5–9 (mild), 10–14 (moderate), 15–19 (moderately severe) and 20–27 (severe) [41]. The Side Effects Rating Scale (SERS) of Asberg assesses the unwanted effects accompanied by antipsychotic drugs weekly, questions around the severity of increased fatigability, headache, insomnia, dizziness, orthostatic syncope, palpitations, tremor, increased tendency of sweating, reduced salivation, constipation, urination disorder, sleepiness, sexual dysfunction, and others. Its scores ranges from 0 (absent) to 3 (among the most severe) [42].

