### Data management and monitoring

The clinical researchers will receive 2 weeks of trial-related training regarding the research content and scale instructions prior to the start of our study. All researchers have completed their courses in Good Clinical Practice. The rater for the HAMD-24 pair, CGI scale, and SERS are licensed and experienced physicians with psychiatric learning backgrounds. The majority of HAMD-24 scale assessment data will be collected by face-to-face joint interviews, with one researcher using the structured interview guide to initiate discussion with the patients, while the other researcher obtains the missing required information if necessary and scores it separately afterward; this procedure is intended to increase the data reliability. After grading, if any controversial items appear, a consensus conference will be held or the patients may even be reassessed on the same day to improve data accuracy. Interviews through video teleconference will be used in some exceptional situations. The CGI scale data will be collected according to the available information through the interview with patient, care-giver, or daily observation while hospitalized. The SERS will be scored based on the information provided by the patients and excludes the symptoms of somatic anxiety from MDD. The self-rated scale PHQ-9 will ensure the patients’ full comprehension of each question in advance. Laboratory tests and instrumental examinations will be conducted in the relevant hospital department. Collected patient data will be recorded on the CRF by assigned clinical researchers. An independent Data Monitoring Committee (DMC) will meet after a group of six participants has completed their final visits to review the ongoing recruitment and protocol compliance, to safeguard the interests of the trial participants, to assess the safety and efficacy of the interventions during the trial and the consistency between the original data and CRF, to ensure that every adverse event is recorded on AER forms and that they are securely stored and to monitor the overall conduction of the clinical trial. An independent clinical research associate will prepare a final report for the principle investigators (PIs), [name] and [name] after the visit.

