### Statistical analyses

The statistical analyses mentioned below will be performed by a bio-statistician not affiliated with our study. Data from CRFs will be computed by two different researchers. Primary results will be based on the intention-to-treat principle. Data for feasibility and safety analysis will be presented as relative frequencies using descriptive statistics. The primary and secondary efficacy outcome measures will use analysis of covariance (ANCOVA) to compare the means between three groups at each time point after adjusting for the fixed factors (gender) and covariates (age, baseline scale score). Multiple comparisons between groups will be performed using the least significant difference (LSD) test. Repeated measures analysis of variance will be performed to determine whether the treatment effects changed over time. The missing values of the efficacy outcome measurements will be managed using the last-observation-carried-forward method. Additionally, sensitivity analysis will be further performed using original data without replacing values missing from the efficacy outcomes.

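### SERS scoring removes only somatic anxiety, so side-effect frequencies for insomnia can include depressive insomnia that was present at entry

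*Protocol article*

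**What the plan says.** Under Study efficacy outcomes, the article describes the Side Effects Rating Scale (SERS) as a measure of unwanted drug effects. It "questions around the severity of increased fatigability, headache, insomnia, dizziness, orthostatic syncope, palpitations, tremor"; from insomnia onward the list reads "insomnia, dizziness, orthostatic syncope, palpitations, tremor, increased tendency of sweating, reduced salivation, constipation, urination disorder, sleepiness, sexual dysfunction, and others". On scoring: "Its scores ranges from 0 (absent) to 3 (among the most severe".

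The same section gives the seven HAMD-24 subsets. Anxiety/somatic symptoms are the first, and the last three are "5) retardation; (6) insomnia; (7) helplessness and worthlessness and hopelessness". Primary efficacy outcome measures applies the reduction rate to the total score and to each subset, so insomnia is part of the primary efficacy measure.

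Data management and monitoring gives the one rule that separates illness from side effect on the SERS: "The SERS will be scored based on the information provided by the patients and excludes the symptoms of somatic anxiety from MDD".

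Safety outcome measures places the SERS among the safety outcomes and has it rated at each evaluation time point, with the schedule in Fig. 2. The feasibility table under Outcomes includes "The occurrence rate of side effects or the adverse events". Statistical analyses says: "Data for feasibility and safety analysis will be presented as relative frequencies using descriptive statistics". In that section, adjustment for the baseline score is stated for the efficacy outcomes only.

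**The concern.** One symptom serves two opposite purposes. Insomnia counts as depression on the HAMD-24 and as an unwanted effect on the SERS. A patient who enters with depressive insomnia and still has it at week 1 can score above zero on the SERS insomnia item although no drug caused it. The authors saw that illness and side effects can be confused, because they remove somatic anxiety. On its wording, however, that removal does not reach insomnia.

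Safety is one of the two stated aims of the pilot (Research objectives), and its results are meant to inform the design of a full-scale trial. If persisting illness enters the SERS frequencies, they overstate side effects in all three arms. If one active arm also relieves depression better, its frequency falls for that reason alone, and a real excess of drug-induced insomnia could be hidden.

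**Working it through.** **Side-by-side reading.** The document has no figure to reproduce, so the first check is whether the stated rules let illness into the SERS.

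1. Is insomnia expected at entry? Yes. Combination therapies provides separately for enrolled patients with mild sleep difficulties and for those with severe insomnia.
2. Does the exclusion cover it? Not on its wording. The rule names somatic anxiety, and the article's own HAMD-24 list keeps anxiety/somatic symptoms (subset 1) apart from insomnia (subset 6).
3. Does the tabulation remove it? Nothing stated does so. Safety data are relative frequencies. Change from baseline (Secondary efficacy outcome measures) and baseline adjustment (Statistical analyses) are stated for efficacy scales.
4. Do other items overlap? Possibly. Sleepiness, sexual dysfunction and increased fatigability can be depressive symptoms, but the article does not say that patients enter with them. The word increased also makes the fatigability item a weaker example.

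**Illustration of size.** All inputs are assumptions, because the documents give none of them:

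- p0, share entering with the symptom as illness: 30%, 50%, 70%
- r, share in whom it resolves: 30% in control; 30%, 50% or 60% in the comparison arm
- d, true drug-caused rate: 10% in both arms

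If any score above zero is counted, and the drug effect is independent of the illness symptom, then

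P(item > 0) = 1 − (1 − p0 × (1 − r)) × (1 − d).

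Example with p0 = 70%. Control: 1 − (1 − 0.7 × 0.7) × 0.9 = 1 − 0.51 × 0.9 = 54.1%. Arm with r = 60%: 1 − (1 − 0.7 × 0.4) × 0.9 = 1 − 0.72 × 0.9 = 35.2%. Difference: 18.9 points, or 0.189 × 14 = 2.6 patients.

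| p0 | r = 30% (control, or any arm with equal resolution) | r = 50% | r = 60% | False advantage over control |
|---|---|---|---|---|
| 30% | 28.9% | 23.5% | 20.8% | 5.4 to 8.1 points |
| 50% | 41.5% | 32.5% | 28.0% | 9.0 to 13.5 points |
| 70% | 54.1% | 41.5% | 35.2% | 12.6 to 18.9 points |

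The true drug-caused rate is 10% in every cell. Two results follow:

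- Inflation does not need unequal efficacy. With equal resolution both arms show 28.9 to 54.1% instead of 10%.
- The between-arm distortion does need it. With equal resolution it is 0; otherwise it is 5.4 to 18.9 points here, about 0.8 to 2.6 of 14 patients.

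The model ignores the hypnotics allowed for severe insomnia, which would change r in all arms.

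**The case against.** The strongest reply is that this is a journal article. How a side-effect scale is tabulated is commonly left to the analysis plan, the case report form or the rater manual, and no sentence says that raw post-baseline SERS scores will be counted as side effects. Fig. 2 is not visible, so a baseline SERS may already be scheduled. Under Harms, physicians judge whether reported discomfort is related to the study drugs, and the SERS raters are experienced physicians with psychiatric backgrounds.

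Part of this stands. Mere silence on a treatment-emergent rule would be no finding, and a baseline rating may exist. What remains is a rule that the article does state and that is too narrow: it separates illness from side effect for one symptom group and leaves out another that the article itself treats as depression. The causality judgement under Harms concerns discomfort that patients report and does not expressly govern SERS scoring.

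A reader might go further and infer that the plan's side-effect rate measures the illness, or that an effective arm will look safer. The documents do not support either as a fact. The occurrence rate in the feasibility table is not said to be computed from the SERS, and the causality judgement bears on it. The between-arm effect depends on raw counting and on a real difference in improvement.

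It is also fair to say that a false gap would be small beside chance. For 54.1% against 35.2% with 14 per arm, the standard error is √(0.541 × 0.459/14 + 0.352 × 0.648/14) = 18 points, and safety is only described, not tested. That limits the harm of the between-arm distortion. It does not remove the inflation within each arm.

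**Conclusion.** The concern holds in limited form. As written, SERS frequencies for insomnia can include depressive insomnia that was present at entry, because the only stated illness exclusion is somatic anxiety and no baseline reference is stated for safety data. Increased fatigability, sleepiness and sexual dysfunction may overlap in the same way, but this is plausible rather than documented.

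If such symptoms are scored, frequencies are too high in all arms. An arm looks safer than another only if its patients improve more. The actual size is unknown: the ranges above rest wholly on assumed prevalence, resolution and drug-caused rates. The point is worth settling before the SERS results are tabulated, since safety is a main aim and a few patients per arm shape the picture.

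**What to change.** Use the SERS rating made before the first infusion, and add one at baseline if Fig. 2 does not already schedule it. Count a SERS item as treatment-emergent only when it is new or its score is higher than the patient's own pre-infusion score. Report these frequencies by arm as the main SERS result, with the raw scores alongside, and state that the rule applies to every SERS item.

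The cost is one tabulation rule and at most one extra rating per patient. There are two downsides. Unchanged baseline symptoms no longer appear in the main SERS frequencies. A drug effect that only maintains a pre-existing symptom, without raising it above its pre-infusion level, would be seen only in the raw scores, which is why these should stay in the report.
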